### Analyses

After 12 weeks of the trial, 3 categories of data, including demographic, clinical risk factor, and active and sedentary behavior data, will have been collected. Regarding descriptive statistics for each indicator, the changes in clinical risk factors during the first 6 weeks, the last 6 weeks, and the entire 12-week trial will be calculated and presented as the means, SDs, and quartiles to show differences. Active and sedentary behavior will be presented as minutes of weekly light, moderate, and vigorous-intensity physical activity, and sedentary time will be obtained from the self-reported GPAQ items. Demographic variables will be presented as sum values or percentages. Additionally, the diagnosis of metabolic syndrome for all groups of participants will be summarized into sums and percentages at each stage according to the definition from a World Health Organization consultation report (high levels of insulin and impaired fasting glucose, together with at least two of the following items: HDL-C concentration less than 35 mg/dL for men [39 mg/dL for women], triglyceride concentration greater than 150 mg/dL, a waist circumference greater than 37 inches, BMI greater than 30 kg/m^2^, systolic blood pressure greater than 140 mm Hg and diastolic blood pressure greater than 90 mm Hg) [4,70].

As it will be adjusted for demographic variables, the linear mixed model, which is recommended in the literature for individually assigned RCTs [75], will be used as an analysis method for determining the effects of the intervention. In cases where participants drop out or are nonadherent, missing data will be handled via multiple imputation techniques. The primary outcome assessed is the change in clinical risk factors for metabolic syndrome, including HDL-C, LDL-C, triglycerides, blood pressure, waist circumference, BMI, impaired fasting glucose, and insulin. The linear mixed model will compare these clinical risk factors across the 3 groups—VR exergame intervention, regular physical activity control, and nonexercise control groups—over three stages. The model will also assess the interaction between groups and time to determine whether the VR exergame intervention has different or additional effects compared with regular physical activity and no physical activity. Adherence to the intervention will be assessed through daily self-report logs for all participants and included as a covariate to account for variations in engagement with the interventions. Additionally, sensitivity analyses will be conducted to examine the potential impact of varying adherence levels on metabolic outcomes. This approach ensures that adherence variations are properly considered when the study’s results are interpreted. In this study, the intervention or control groups are fixed factors, and demographic factors would be considered as random factors for accommodating variabilities within or between participants. All available data will be imported into Stata (version SE 15.1; Stata Corp) for analysis, and the significance level will be set at *P*<.05. As this is an exploratory pilot study, the primary objective is to assess feasibility and gather preliminary data. Given the lack of prior studies using immersive VR exergames in this context, conducting a power analysis would be speculative. The focus of this pilot is to generate effect size estimates and assess practical considerations, which will inform the design of a future, fully powered RCT. In the larger RCT, a formal power analysis will be conducted using the data generated from this pilot study.

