VR^d^ exergame intervention group	Manual booklet Demographic questionnaire GPAQ^e^ Meta Quest 2 set Recording sheet of exergaming time	GPAQ Recording sheet of exergaming time	—^f^
Regular physical activity control group	Manual booklet Demographic questionnaire GPAQ	GPAQ	Meta Quest 2 set
Nonexercise control group	Manual booklet Demographic questionnaire GPAQ	GPAQ	Meta Quest 2 set

^a^Start of the trial.

^b^Week 6 of the trial.

^c^End of the trial.

^d^VR: virtual reality.

^e^GPAQ: Global Physical Activity Questionnaire.

^f^Not applicable.

All participants will be asked to visit the data collection center in three stages for data collection and experimental material allocation. The self-reported GPAQ questionnaire will be completed by all participants at home, as it is a convenient at-home format for exploring impacts on active and sedentary behavior. The VR exergame intervention group will record the frequency and duration of their exergaming sessions, the regular physical activity control group will track their daily exercise routines, and the nonexercise control group will report any physical activities they perform beyond their baseline. Participants will be asked to bring all self-report sheets to the data collection center at stages 2 and 3. Coordinators will collect and summarize all the completed questionnaires and recording sheets for data processing. Major clinical risk factors are objectively measured from participants’ metabolic syndrome biomarkers, which are operated by professional nurses at the data collection center (cooperative clinic). Since there is a fasting biomarker for testing metabolic syndrome, all participants are required not to consume any food or drink 12 hours before blood sample collection in the morning. After the major clinical risk factor data from all the participants for the entire trial are collected, the experiment coordinators will visit and obtain the data from the data collection center.

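### Self-reported adherence, measured after randomisation and recorded differently in each arm, is a covariate in the model for the intervention effect and can bias the VR versus nonexercise comparison

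*Protocol article*

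**What the plan says.** The Analyses section of the protocol article names a linear mixed model that "will be used as an analysis method for determining the effects of the intervention". On the outcome it states: "The primary outcome assessed is the change in clinical risk factors for metabolic syndrome", followed by eight risk factors. On the contrast of interest it states: "The model will also assess the interaction between groups and time to determine whether the VR exergame intervention has different or additional effects", relative to each of the two control groups.

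The same section says adherence will be "assessed through daily self-report logs for all participants and included as a covariate to account for variations in engagement with the interventions". The next sentence reads: "Additionally, sensitivity analyses will be conducted to examine the potential impact of varying adherence levels on metabolic outcomes". The sensitivity analyses are therefore an addition, and the covariate belongs to the main model. The section describes no model-based comparison without adherence.

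The Study Procedure section says what each arm logs. "The VR exergame intervention group will record the frequency and duration of their exergaming sessions"; the regular physical activity arm tracks its daily exercise; and "the nonexercise control group will report any physical activities they perform beyond their baseline". Under Intervention and Control Groups, the VR arm is asked for at least 150 minutes a week, the regular activity arm for a routine of similar duration and intensity, and the nonexercise arm gets no exercise instruction.

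**The concern.** There are three separate difficulties.

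- **Mediation.** Minutes of exercise are a consequence of allocation and the route by which the exercise arms should change the biomarkers. Holding them fixed removes the part of the effect that travels through them.
- **Confounding.** Within an arm, people who log more may also be more motivated and improve for other reasons. Conditioning on the log brings that difference into a comparison that randomisation had protected.
- **Meaning.** A high value indicates following the assignment in the two active arms and departing from it in the nonexercise arm. A single coefficient across the three has no clear interpretation.

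At stake is what the model's group comparison estimates. The article says the pilot is to generate effect sizes for the power analysis of a larger trial, so a distorted estimate would carry into that design.

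**Working it through.** The article gives no effect size, SD or power, so there is no planned figure to reproduce. The only stated input is 40 per arm (3 × 40 = 120). Everything else here is an assumption. A negative difference means improvement.

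**1. Week-12 regression**

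Assumed minutes per week: mean 120 (SD 50) in both active arms and 20 (SD 30) in the nonexercise arm. The difference in means is d = 100. The within-arm variances sum to 2500 + 2500 + 900 = 5900. Outcome SD is about 1.

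Adjusted difference = total difference − s × d, where s is the pooled within-arm slope of outcome on minutes.

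- *Fully mediated.* s = -0.0048, total = -0.48. Adjusted: -0.48 + 0.0048 × 100 = 0.00.
- *Half mediated.* s = -0.0025, direct effect -0.25, total = -0.50. Adjusted: -0.50 + 0.25 = -0.25.
- *Standard error.* Adjusted: √(2/40 + 100²/(39 × 5900)) = √(0.0500 + 0.0435) = 0.306. Simulated unadjusted value: 0.228. The ratio is 1.34, an increase of 34%.
- *True null.* Motivation has correlation 0.3 with improvement and r with minutes. Then s = -0.3 × r × (50 + 50 + 30)/5900, and the adjusted difference is 0.3 × r × 130 × 100/5900 = 0.661 × r.

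| r | Spurious difference (SD) | Type I error |
|---|---|---|
| 0.3 | +0.20 | 10% |
| 0.5 | +0.33 | about 20% |
| 0.7 | +0.46 | 32% |

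A repeat with 10,000 simulated trials gave type I errors of 10%, 19% and 34%, so the last figure is about one third.

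*VR versus regular activity.* Mean minutes are equal by assumption, so d = 0 and adjustment does not shift this contrast. It would shift by s times whatever difference arose.

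**2. Mixed model closer to the plan**

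Three visits, random intercept, group × time, 40 per arm, 120 simulated trials per scenario. Assumed: minutes 120/120/20 (SD 40/40/20), between-participant SD 0.8, residual SD 0.6, and a total VR versus nonexercise effect of about -0.5 units at week 12 (zero in the null scenario). Entries are the mean week-12 group × time estimates for VR versus nonexercise.

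| Scenario | No adherence | (a) Stage-specific adherence | (b) Average adherence × time, or change-score model | (c) Time-constant main effect, complete data |
|---|---|---|---|---|
| Full mediation | -0.46 | -0.11 | +0.02 | -0.46 |
| Half mediation | -0.45 | -0.26 | -0.25 | -0.45 |
| Full mediation plus confounder | -0.47 | -0.01 | +0.35 | -0.47 |
| True null plus confounder | 0.01 | 0.11 | 0.30 | 0.01 |

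The mean SE is about 0.19 without adherence, 0.23 to 0.24 in (a) and 0.35 to 0.38 in (b). In (c) the SE is unchanged, but the baseline group difference, truly 0, is estimated as +0.30 under full mediation and +0.13 under the confounded null.

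The article does not say which form is meant. It defines the primary outcome as change, and it issues the VR recording sheets separately for weeks 0 to 6 and 7 to 12. Forms (a) and (b) are therefore plausible.

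**The case against.** The strongest reply is that the plan tests group × time in a mixed model, and that a participant-level adherence covariate entered only as a main effect leaves this contrast alone. That is correct for form (c) with complete data. A reader might infer that any use of the covariate destroys the randomised estimate; the article does not support that, because it does not state the form. But it does not restrict itself to (c) either, and even there the group main effect is distorted.

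A reader might also infer that neither comparison with a control is answered. The shown bias concerns VR versus nonexercise. The regular activity arm is planned to match VR in duration and intensity, and with equal logged activity that contrast does not move.

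Adherence might also be scored relative to each arm's assignment rather than in minutes. The scale is not defined, and such a score would depend less on arm. It would still be measured after randomisation and open to confounding by motivation.

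Finally, this is an exploratory pilot with feasibility as its stated objective, and the article separately plans descriptive changes for each period without adherence adjustment. That lowers the harm. It does not remove it, because the effect estimates are meant to feed the later trial and the Discussion promises a significance statement against both controls.

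**Conclusion.** The point stands in conditional form. A post-randomisation variable, largely determined by arm and recorded differently in each, is placed in the only model named for the intervention effect. This is a stated rule, not a detail left open.

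If adherence is stage-specific, interacts with time, or enters a change-score model, the VR versus nonexercise contrast is biased: by all of the effect under full mediation in the week-12 regression, by about half under half mediation, and away from zero under a null with confounding by motivation. If it is a time-constant main effect with complete data, only the group main effect is affected. The VR versus regular activity contrast is at risk only to the extent that logged activity differs between those arms.

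The sizes rest on assumed minutes, SDs, mediation shares and correlations, none of which is in the article; the null result is especially sensitive to the correlation between motivation and minutes. The mechanism does not depend on those values.

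**What to change.** - Delete adherence from the primary model. Compare participants as randomised, with group, time and group × time, adjusted only for variables measured at baseline (the outcome's baseline value, age, gender).
- Report adherence descriptively by arm, as a feasibility result, stating what each arm's log records. Table 2 issues a recording sheet only to the VR arm, while Analyses relies on daily logs from everyone; reconcile the two.
- The article already plans that "sensitivity analyses will be conducted to examine the potential impact of varying adherence levels on metabolic outcomes". Keep this as a separate, labelled exploratory analysis, and state that it is not read as the causal effect of VR, because adherence levels are confounded by motivation.
- Do not substitute a complier-average estimate that splits participants at 150 min/week. Under the assumed N(120, 50), only 27% of the VR arm reaches 150, and those below it still benefit, which breaks the exclusion restriction. In the fully mediated scenario the estimator is about -0.48/0.274 = -1.75 SD, against -0.77 SD in those who do reach 150.

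The cost is a wording change in Analyses. No new data or visits are needed, and under forms (a) and (b) the standard error falls.

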## Methods

### Study Design

RCTs, a top-level research methodology in the area of evidence-based medicine [47], have played a significant role in evaluating the effects of lifestyle changes on metabolic syndrome [48-50]. This protocol is a longitudinal pilot study that uses a 3-arm parallel-group RCT to examine the interventional efficacy of an at-home immersive VR exergame on several clinical risk factors of metabolic syndrome among office workers. On the basis of prior research on exercise and physical activity interventions [48,51], a 12-week duration was selected for this trial, as it is a commonly used period for evaluating the efficacy of interventions targeting metabolic syndrome. Several clinical risk factors for metabolic syndrome, as well as active and sedentary behavior, will be monitored in three stages during this 12-week trial. Stage 1 will be at the start of the trial, Stage 2 at week 6, and Stage 3 at the end of the trial. The therapeutic effects of the at-home immersive VR exergame intervention for metabolic syndrome will be evaluated by comparing these risk factors among three groups: the VR exergame intervention group, the regular physical activity control group, and the nonexercise control group. The study follows two checklists: the CONSORT-EHEALTH (Consolidated Standards of Reporting Trials Statement for Randomized Controlled Trials of Electronic and Mobile Health Applications and Online TeleHealth) [52] and the SPIRIT (Standard Protocol Items: Recommendations for Interventional Trials; Multimedia Appendices 1 and 2) [53,54].

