### Ethical Considerations

This study was approved by the Institutional Ethics Committee of Guangzhou University, China (2024-112; September 25, 2024). Initially, potential participants will be provided with basic information regarding the benefits of exercise for health and immersive VR exergames. Subsequently, interested individuals will receive a detailed explanation of the study process, and they will be asked to sign the informed consent and assent forms. In addition, some personal information is required during this trial, including name, age, gender, email address, home address, and phone number for the purpose of marking data, sending the results of blood tests and diagnosis of metabolic syndrome, or analyses (eg, as covariates). All participant information will be collected directly by the experiment coordinator (JZ) to ensure the privacy of their personal information. Strict measures will be implemented to manage and store all the collected data. To compensate for participation, participants will be rewarded with RMB 150 (approximately US $21) for completing each stage, whereas participants who complete all the processes of the trial will be rewarded with RMB 500 (approximately US $71). All incentives will be sent via a registered postal cash envelope. For visiting the data collection center at each stage, transportation fees will also be reimbursed.

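### The mixed model gives the random role to age and gender and names no participant effect, so as written it misstates the standard error of the group-by-time contrast

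*Protocol article*

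**What the plan says.** Study Design sets three measurement occasions: "Stage 1 will be at the start of the trial, Stage 2 at week 6, and Stage 3 at the end of the trial". Table 1 has all eight clinical risk factors measured at each of them, and age and gender recorded once, at stage 1.

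The Analyses section gives the outcome and the model. On the outcome: "The primary outcome assessed is the change in clinical risk factors for metabolic syndrome". On the test of interest: "The model will also assess the interaction between groups and time". On the structure of the model: "the intervention or control groups are fixed factors, and demographic factors would be considered as random factors for accommodating variabilities within or between participants".

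Two other places give the demographics a different role. Earlier in the Analyses section the model is introduced with "As it will be adjusted for demographic variables, the linear mixed model". Ethical Considerations lists age and gender among the personal information collected for several purposes, including "or analyses (eg, as covariates". Both describe ordinary covariates.

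The article names no participant random effect, clustering by participant or residual covariance over the stages.

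**The concern.** A linear mixed model for repeated measures has to represent the fact that three values from one person resemble each other more than values from different people. A participant random effect does this, as does a residual covariance within participant. The article gives the task to age and gender instead. Neither identifies a participant, both are fixed over the trial, and both are shared by many of the 120 people. Gender also has too few levels for its variance to be estimated usefully.

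This goes beyond brevity. An article may leave the covariance structure to the analysis plan, but this one states a random structure and assigns it to the wrong variables. It also contradicts its own description of the demographics as adjustment variables. A plan that named a participant effect would have to depart from the published sentence.

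Two things are at stake: the precision claimed for the between-group difference in change, and the variance estimates that the pilot is meant to supply. The Analyses section says that the larger trial's power calculation will use this pilot's data.

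**Working it through.** **Inputs.** From the protocol article: 40 participants per group (Study Procedure), three stages (Study Design), significance level 0.05 (Analyses; two-sided assumed, as sidedness is not stated). The article gives no standard deviation, effect size, power or within-person correlation, so there is no figure of its own to reproduce. Assumptions: unit standard deviation, compound symmetry, and within-person correlation rho of 0.3 to 0.8.

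**Change from stage 1 to stage 3, difference between two arms.** The variance of one person's change is 2(1 − rho), so
- correct SE = sqrt(4(1 − rho)/40);
- SE with no person effect = sqrt(4/40) = 0.316;
- ratio = 1/sqrt(1 − rho).

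For a true difference that the correct model detects with 80% power, the power without a person effect is Φ((1.960 + 0.842) × sqrt(1 − rho) − 1.960). At rho 0.5 this is Φ(2.802 × 0.707 − 1.960) = Φ(0.021) = 0.51.

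**Arm difference averaged over the three stages.**
- correct SE = sqrt(2(1 + 2rho)/(3 × 40));
- SE with no person effect = sqrt(2/(3 × 40)) = 0.129;
- actual type I error = 2(1 − Φ(1.960/sqrt(1 + 2rho))).

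| rho | Change: correct SE | Change: SE without person effect | Ratio | 80% power becomes | Actual level of nominal 0.05 change test | Average: correct SE | Average: SE without person effect | Actual type I error, average |
|---|---|---|---|---|---|---|---|---|
| 0.3 | 0.265 | 0.316 | 1.20 | 65% | 0.019 | 0.163 | 0.129 | 12% |
| 0.5 | 0.224 | 0.316 | 1.41 | 51% | 0.006 | 0.183 | 0.129 | 17% |
| 0.7 | 0.173 | 0.316 | 1.83 | 34% | 0.0004 | 0.200 | 0.129 | 21% |
| 0.8 | 0.141 | 0.316 | 2.24 | 24% | below 0.0001 | 0.208 | 0.129 | 22% |

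**Do random age and gender repair this?** The closed forms assume no person effect at all. A random age factor does induce some correlation among people of the same age, including between a person's own visits. The model as written (random intercepts for age in years and for gender, no participant term) was therefore fitted by REML to 60 simulated trials at each of two correlations, with ages assumed uniform over 22 to 45.

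| rho | Contrast | Correct SE | Mean SE, model as written | Mean SE, participant intercept |
|---|---|---|---|---|
| 0.5 | Change | 0.224 | 0.303 | 0.224 |
| 0.8 | Change | 0.141 | 0.302 | 0.141 |
| 0.5 | Average | 0.183 | 0.130 | 0.180 |
| 0.8 | Average | 0.208 | 0.131 | 0.210 |

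The change SE is still 0.303/0.224 = 1.35 and 0.302/0.141 = 2.14 times too large, against 1.41 and 2.24 in the closed form. The demographic random factors recover very little; a participant intercept recovers the correct values.

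**Planning the larger trial.** Without a person effect the residual variance absorbs the between-person variance. A sample size for change computed from that residual variance is inflated by 1/(1 − rho): 1.4-fold at 0.3, 2-fold at 0.5, 3.3-fold at 0.7 and 5-fold at 0.8.

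**The case against.** The strongest reply is that this is a drafting slip. The sentence gives the purpose of the random part in terms of variability within and between participants, which is what a participant effect does, and the references to adjustment and covariates point the same way. The analysis plan, not shown, may specify the model properly. This stands as a reading of intent, so the consequences above are conditional on fitting the model as written. It does not rescue the sentence, which still names the wrong variables; the correction is the same either way.

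Several stronger readings are tempting, and the documents do not support them.

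- *The primary question is exposed to false positives.* It is not. The stated outcome is change and the stated test is the group-by-time interaction, which becomes conservative. With reference coding in an interaction model, the group coefficient is the baseline difference; its SE is sqrt(2/40) = 0.224 with or without a person effect, so it keeps its 5% level. Inflation arises only for a visit-averaged group contrast, which the article does not single out.
- *Stage is missing from the model.* The article compares the groups over the three stages and plans a group-by-time interaction, so time is in the model.
- *The repeated measures are treated as wholly uncorrelated.* This is slightly too strong, because random age gives weak correlation.
- *A two-level random factor cannot be fitted.* It can, but its variance is very poorly estimated.
- *The trial loses a planned 80% power.* The article makes no power calculation. The 80% is only a yardstick.

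It is also fair that this is an exploratory pilot and that, with complete balanced data, the point estimates of between-arm change do not depend on the random structure. The standard errors, intervals, P values and variance components do, and the variance estimates are among the results that the larger trial would need.

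**Conclusion.** The point holds as a misstatement of the model. The Analyses section gives age and gender a job that they cannot do, names nothing that can do it, and contradicts its own description of the demographics as adjustment variables. Followed literally, it makes the SE of the change contrast about 1.2 to 2.2 times too large for within-person correlations of 0.3 to 0.8. Random age and gender reduce this only slightly in simulation. The error on the primary question is lost power and over-wide intervals, together with distorted variance estimates for the next trial. Type I inflation of about 12% to 22% is confined to visit-averaged group contrasts, if any are reported.

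The size rests on assumed correlations, compound symmetry and literal fitting; the simulation also rests on an assumed age distribution. The direction of each error holds for any positive within-person correlation.

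**What to change.** Replace the sentence on fixed and random factors. State that the fixed effects are group, stage, group by stage, age and gender, and that the repeated measurements are handled by a participant random intercept or by a residual covariance over the three stages within participant. Delete the demographic random factors. The choice between the two ways of handling the correlation can be left to the analysis plan; either removes the error.

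The cost is one sentence. No new data are needed, the planned software fits the model, and the change should be made before the data are analysed.

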**Objective:**

This exploratory study aims to examine the interventional efficacy of at-home immersive VR exergames on metabolic syndrome biomarkers among office workers. Additionally, it seeks to investigate the impacts of at-home immersive VR exergames on the active and sedentary behaviors of office workers.

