## Discussion

### Principal Findings

Our findings will reveal whether the clinical risk factors for metabolic syndrome within the intervention group significantly improved after a 12-week exergaming intervention compared with those in the two control groups. The increase in the time engaged in physical activity (all types of light, moderate, and vigorous intensity) and the decrease in the time spent in sedentary behavior will also be evaluated.

The phenomenon of physical inactivity among employed adults has been occurring increasingly worldwide because of the development of society and technology in recent decades [16,17]. Consequently, the population of employed adults at risk for metabolic syndrome is growing across the globe [14,15]. Several primary factors, such as a lack of motivation, weather restrictions, and busy schedules for work, social lives, and family, have been reported as key barriers to physical activity [34]. Notably, at-home immersive VR exergames can provide several advantages to address these barriers to physical inactivity for employed adults. However, to our knowledge, few studies have explored the health effects of immersive exergames. This study is the first RCT and aims to examine the effectiveness of at-home immersive VR exergame interventions for improving metabolic syndrome. Our hypotheses were based on several advantages of at-home immersive VR exergames. The first benefit to exergames is engagement and enjoyment, as various types of motivational affordances (eg, points, leaderboard, and badges) were found within the gaming process along with several positive psychological effects (eg, joyfulness) [76]. The second advantage is the convenience of at-home exercise, which can mitigate weather restrictions and fit into a flexible schedule. In addition, exergames also have positive impacts on both physical health and cognition [77], which may offer pathways to improve rehabilitation and wellness [41]. Although these positive results have been reported, there is also some evidence that these positive impacts from exergames may be temporary [78].

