### Conclusions

The use of at-home immersive VR exergames for improving metabolic syndrome is an emerging topic for promoting physical activity related to cardiometabolic health. The primary aim of this proposed study is to assess the feasibility and preliminary effects of an at-home immersive VR exergame intervention on the clinical risk factors for metabolic syndrome. The results of using at-home immersive VR exergames may contribute to promoting office workers’ health conditions and help reduce the burden of metabolic syndrome risk among a large and increasingly sedentary population. These results will inform the design and implementation of a larger-scale, fully powered RCT. This exploratory pilot RCT will provide data regarding the intervention’s practicality and initial effectiveness, which will guide future research efforts.

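### Feasibility is half of the stated primary objective but has no outcome; the only primary outcome is eight biomarkers tested at P<.05, and their noisy pilot effects are likely to size the next trial

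*Protocol article*

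**What the plan says.** The protocol article states its purpose in two ways.

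- **Feasibility plus preliminary information.** Analyses: "the primary objective is to assess feasibility and gather preliminary data". Conclusions: "The primary aim of this proposed study is to assess the feasibility and preliminary effects of an at-home immersive VR exergame intervention".
- **Efficacy.** The Abstract objective reads "This exploratory study aims to examine the interventional efficacy of at-home immersive VR exergames on metabolic syndrome biomarkers among office workers" and does not mention feasibility. Study Design likewise speaks only of efficacy.

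The primary outcome follows the second version: "The primary outcome assessed is the change in clinical risk factors for metabolic syndrome, including HDL-C, LDL-C, triglycerides, blood pressure, waist circumference, BMI", with fasting glucose and insulin completing a list of eight. Analyses compares these across three groups and three stages in a linear mixed model, with significance at P<.05. Principal Findings says the results will show "whether the clinical risk factors for metabolic syndrome within the intervention group significantly improved after a 12-week exergaming intervention", judged against both control groups.

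Table 1 lists demographics, clinical risk factors, and active and sedentary behaviors. None is designated a feasibility measure. Adherence logs are kept, but Analyses uses them only as a model covariate and in sensitivity analyses of the metabolic outcomes.

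Analyses declines a power calculation as speculative, gives estimating effect sizes as a focus of the pilot, and adds: "In the larger RCT, a formal power analysis will be conducted using the data generated from this pilot study".

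**The concern.** A primary objective needs an outcome that can answer it. Here the article names both an objective and a primary outcome, and they match only in part. Whatever happens, the feasibility conclusion would rest on evidence chosen afterwards.

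The biomarker half is set up as a significance test although the article says it has no basis for a power statement. A significant result on one of eight markers could be over-read, and a nonsignificant one is hard to interpret.

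The pilot's effect estimate is also likely to feed the sample size of the larger trial. An estimate from 40 per arm is imprecise for that use, and it is biased upward if the larger trial is planned only after a significant pilot.

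**Working it through.** **Setting the statements side by side**

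| Element | Feasibility | Preliminary data or effects |
|---|---|---|
| In the primary objective (Analyses, Conclusions) | yes | yes |
| In the Abstract objective and Study Design | no | yes, as efficacy |
| Has a primary outcome | no | yes, eight biomarkers |
| Role of adherence | none as an outcome | covariate, sensitivity analysis |
| Planned reading | none stated | significantly improved or not |

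**The article's own figure.** 3 arms × 40 = 120, which agrees with the stated total. No effect size, SD, power or precision target is given, so there is no derivation to reproduce.

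**Inputs.** n = 40 per arm and the 0.05 level are from the article. Assumed, because the article does not give them: two-sided testing, no dropout, a true effect of 0.3 SD, and a correlation r between baseline and week 12, shown as a range. SD means the between-person SD at one visit. The week-6 visit is ignored.

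**Precision of one pairwise difference.** SE = √(2/40) × √(1 − r²), and the half-width is t(78) × SE with t = 1.991.

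- r = 0: SE 0.2236; half-width 1.991 × 0.2236 = 0.445 SD
- r = 0.5: SE 0.1936; 0.39 SD
- r = 0.7: SE 0.1597; 0.32 SD
- r = 0.9: SE 0.0975; 0.19 SD

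Power of the pilot at 0.3 SD is 26%, 33%, 46% and 86% respectively (two-sample t test).

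**Sizing the next trial only from significant pilot estimates** (normal approximation).

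1. Chance of a significant positive estimate: p = 1 − Φ(1.96 − 0.3/SE).
2. Median significant estimate: m = 0.3 + SE × z, where z has upper-tail area p/2.
3. Next trial's n per arm for 80% power: 2(1 − r²)(1.96 + 0.84)²/m², with (1.96 + 0.84)² = 7.849 from unrounded quantiles.
4. Its true power: Φ(0.3/√(2(1 − r²)/n) − 1.96).

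| r | p | m (SD) | n per arm, unrounded | n needed at 0.3 SD | true power |
|---|---|---|---|---|---|
| 0 | 0.268 | 0.3 + 0.2236 × 1.107 = 0.548 | 52.3 | 174.4 | 34% |
| 0.7 | 0.468 | 0.3 + 0.1597 × 0.727 = 0.416 | 46.3 | 89.0 | 52% |
| 0.9 | 0.868 | 0.3 + 0.0975 × 0.166 = 0.316 | 29.8 | 33.1 | 76% |

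True power falls as the pilot estimate rises, so the power at the median estimate is the median power. At an assumed true effect of 0.5 SD with r = 0, it is 63%.

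**Multiplicity.** With eight independent tests the chance of at least one false positive is 1 − 0.95⁸ = 34%. At assumed common correlations of 0.3, 0.5 and 0.8 it is about 30%, 25% and 16%.

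**Feasibility at this size.** A rate of 30/40 = 75% has a 95% Wilson interval of 60% to 86%, so a feasibility proportion is usefully estimable in one arm.

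**The case against.** **The objective is not feasibility alone.** Both statements of it add preliminary data or effects, which the biomarkers serve directly. This stands. A reader might infer that the pilot cannot answer its own question; that is true only of the feasibility half.

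**A condensed article may leave progression thresholds to the full protocol.** This stands too. The full protocol is not shown, so missing go or stop criteria are not a finding. The mismatch remains, because the article itself states both the objective and the primary outcome.

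**The unadjusted figures are not for the planned analysis.** Every biomarker has a baseline value and a mixed model is planned. At r = 0.9 the pilot is fairly precise and the next trial's shortfall small. The results must therefore be read as a range over r, and imprecision is not shown for every biomarker.

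**The pilot data could supply SDs and attrition instead of an effect.** They could. But the stated focus on effect sizes, read with the sentence on the later power analysis, makes use of the effect size likely, though not certain. Nothing says that the larger trial depends on a significant pilot, or that a nonsignificant result would count as failure.

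**Pilots need no power calculation.** Agreed, and its absence is not the fault. The difficulty is keeping a significance reading without one.

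**Conclusion.** The contradiction is established from the article's own text: feasibility is part of the primary objective, no outcome addresses it, and the primary outcome, the P<.05 rule and the planned reading all concern efficacy. Confidence in this is high.

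The sizing consequence is conditional. It requires that the pilot effect is used to size the larger trial, that only significant estimates are carried forward, and that the true effect is about 0.3 SD. Median true power is then about 34% unadjusted, 52% at r = 0.7 and 76% at r = 0.9. A reader might take 34% as the forecast for the next trial; it is the least favorable end of an assumed range, and the article fixes neither the effect size nor r. The direction of the bias holds across the range; its size does not.

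The trial can run as designed, but objective, primary outcome and interpretation should be reconciled first.

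**What to change.** 1. **Name feasibility outcomes.** Retention at week 12 comes from stage attendance. The share of each exercise arm logging at least 150 minutes per week comes from the exercise records. Study Procedure says the regular-activity arm tracks its routine, but Table 2 lists a recording sheet only for the VR arm, so these should be aligned.
2. **Add simple counts:** people emailed, people consenting, and reasons for withdrawal. VR sickness is named as a limitation, but no record of it as a reason for stopping is described. If the full protocol already holds feasibility measures or progression thresholds, cite them.
3. **Relabel the biomarkers as preliminary efficacy.** Report between-group differences with 95% confidence intervals and drop the significance reading in Principal Findings. Use the same objective in the Abstract, Study Design, Analyses and Conclusions.
4. **Replace the sentence on the later power analysis.** State that the future trial will be sized on a minimum important difference, with the pilot supplying SD, within-person correlation and attrition.

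The cost is wording changes, a matching registry update and minor extra record-keeping; it is not quite true that nothing new need be recorded. The trial also gives up a formal efficacy claim. Sample size, visits and blood tests are unchanged.
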